## Results

Quantitative data analysis will be conducted using Stata software [67] and R statistical software [68]. Initial analyses will involve inspecting frequency distributions to identify outlying values and skewed variables requiring transformation. Descriptive analyses will provide means, medians, or prevalence of risk factors with associated confidence intervals. Analytic comparisons of pilot cohort drop-outs versus retained subjects will be done using multivariate analysis of variance (MANOVA) for normally distributed continuous variables with log10 (X+1) transformations on skewed behavioral variables, and chi-square tests for categorical variables and Wilcoxon tests for ranked data, with significance levels adjusted for multiple testing.

For the PrEP, CCT, and HIV-positive cohorts, changes over time in risk behaviors will be estimated focusing on initial change (baseline vs 6 months) and delayed change or persistence of initial effects (6 months vs 12 months). We anticipate minimal missing data due to use of CAPI and SMS/USSD data. The primary goal of the longitudinal cohorts is to provide data needed to describe the feasibility of PrEP, ART, and CCT, including medication adherence and school attendance over time. Levels of and changes in adherence and school attendance will be presented graphically, for example, with box plots at each assessment point and trajectory plots. For a detailed analysis plan, see Multimedia Appendix 2.

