#### Cohort Follow-Up Schedules

Participants who attend the mobile MP3 Youth events will be enrolled into 4 cohorts which will be followed up for a period of 12 months via unstructured supplementary service data (USSD) and SMS text message (short message service, SMS) surveys and/or in-person computer-assisted personal interview (CAPI) surveys. The PrEP cohort will be followed up monthly for the first 6 months and every 3 months for the remaining 6 months in a mixture of in-person clinical visits and SMS and USSD surveys to facilitate adherence and conduct laboratory assessments (for HIV and pregnancy). The CCT cohort will be followed up every 3 months (0, 3, 6,9,12 months) for 12 months using an in-person CAPI and school registers checked for attendance. The HIV-positive cohort will also be followed up at intervals of 3 months via SMS and USSD surveys. A random subset of the HIV-negative youth who agree to be called in one year will receive a phone call to assess their HIV retesting behaviors and intentions. The HIV-positive cohort will undergo a clinical assessment at baseline and at month 12 (CD4 and viral load). The CCT cohort will undergo a clinical assessment at baseline and at month 12 (HIV testing and counseling and pregnancy testing). We will administer SMS and/or USSD and CAPI surveys to the cohorts to assess longitudinal self-reported behaviors. During all clinical/laboratory assessments, adverse events will be assessed.

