### Data Collection

This section of the protocol outlines the components that need to be included in order to collect and evaluate the cross-sectional and longitudinal data required to measure the pilot study outcomes. All MP3 Youth mobile event participants who are eligible, consent, and register for MP3 Youth will be required to complete a baseline behavioral CAPI survey and an exit acceptability interview. Participants who are eligible and enrolled in a sub-cohort will be required to complete SMS/USSD mobile phone surveys every month (PrEP cohort) or every 3 months (CCT and HIV-positive cohort). Participants in the PrEP cohort will be required to complete monthly clinical/laboratory visits for the first 6 months and every 3 months thereafter. The following sections describe the specific types of data that will be collected and the suggested data platforms to be implemented.

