#### Behavioral Baseline Interview

The behavioral survey will be a staff-administered CAPI at the mobile events. For sensitive questions (which will be identified in the survey), youth will be instructed that they can tap on the answer with the tablet facing away from the interviewer and the answer will not be visible after entry; this incorporates elements of “ballot box response” or *audio computer-assisted self-interview* (ACASI) approaches while reducing issues around lack of literacy and unfamiliarity with tablet computers [62].

The CAPI will collect the following types of information, including but not limited to the types of services the participant is most interested in accessing: (1) basic demographic information, (2) sexual risk behaviors, (3) HIV risk behaviors, (4) attitudes and/or knowledge about HIV transmission and prevalence, (5) knowledge and acceptability of specific HIV prevention interventions, (6) knowledge and acceptability of family planning methods, and (7) attitudes towards the delivery of services (collected at the exit interview).

The CAPI will provide data that will lead to a better understanding of the combination HIV prevention interventions and prevention behaviors of youth. The responses will help determine the package of services for which the participant is eligible.

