#### Follow-Up Text Message and Unstructured Supplementary Service Data Survey

Using the EchoMobile platform, study staff will make SMS/USSD text contact using an agreed-upon code, to ensure the phone user is the study participant. Staff will then wirelessly transfer airtime, so the cohort participant can send surveys using SMS/USSD [63]. The SMS/USSD survey will be a brief 10-question survey tailored to the cohort population. The surveys will be short to reduce barriers to completion. The responses will be analyzed to assess change in behavior over time as a part of the longitudinal cohort.

The SMS survey will collect information that includes but is not limited to (1) sexual risk behaviors; (2) school attendance (for CCT cohort); (3) adherence barriers and facilitators (PrEP and HIV-positive cohort); and (4) status disclosure (HIV-positive cohort).

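### In the HIV-positive cohort, and probably the PrEP cohort, the baseline-to-6-month change in risk behavior mixes a change of survey mode with time; for the CCT cohort the follow-up mode is contradictory.

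*Protocol article*

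**What the plan says.** The Results section sets two contrasts for the PrEP, CCT and HIV-positive cohorts: "changes over time in risk behaviors will be estimated focusing on initial change (baseline vs 6 months") and then "delayed change or persistence of initial effects (6 months vs 12 months"). It does not name the instrument that supplies each time point.

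The baseline instrument is described under Behavioral Baseline Interview: "The behavioral survey will be a staff-administered CAPI at the mobile events". Sexual risk behavior is among its topics. For sensitive questions, participants are told that "they can tap on the answer with the tablet facing away from the interviewer and the answer will not be visible after entry".

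The follow-up instrument is described in the section on text message and USSD surveys: "The SMS/USSD survey will be a brief 10-question survey tailored to the cohort population". Sexual risk behavior is among its topics, and its answers are to be analyzed for behavior change.

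The mode by cohort is given in two places:
- **HIV-positive.** Cohort Follow-Up Schedules: "The HIV-positive cohort will also be followed up at intervals of 3 months via SMS and USSD surveys". Data Collection agrees.
- **PrEP.** Cohort Follow-Up Schedules combines in-person clinical visits with SMS/USSD surveys. Data Collection requires a monthly SMS/USSD survey and separate clinical visits.
- **CCT.** Cohort Follow-Up Schedules has visits at 0, 3, 6, 9 and 12 months "using an in-person CAPI and school registers checked for attendance". Data Collection requires "SMS/USSD mobile phone surveys every month (PrEP cohort) or every 3 months (CCT and HIV-positive cohort").

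**The concern.** If the baseline answer is given to a tablet in the presence of staff at a mobile event and the 6-month answer is sent by text from a phone, then time, mode, setting and questionnaire length all change together. Sexual risk items are sensitive, and the article itself treats the manner of asking as relevant, since it adds private answer entry at baseline. A shift in reporting would then appear in the baseline-to-6-month estimate as a change in behavior.

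The abstract names risk compensation as something the longitudinal cohorts are to assess, and the Discussion expects information on behavioral change over time. The Limitations section acknowledges that there is no comparator. No concurrent group could therefore reveal a mode shift, which could mimic risk compensation or hide it.

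For the CCT cohort the difficulty comes earlier: the article does not settle which mode is used after baseline.

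**Working it through.** **Step 1. Mode at each end of the first contrast.**

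| Cohort | Baseline | 6 months | Same mode? |
|---|---|---|---|
| HIV-positive | Staff-administered CAPI, private entry for sensitive items | SMS/USSD | No, on the evident reading |
| PrEP | As above | SMS/USSD survey or in-person visit; source of the risk value not fixed | Probably not |
| CCT, per Cohort Follow-Up Schedules | CAPI | In-person CAPI | Yes |
| CCT, per Data Collection | CAPI | SMS/USSD | No |

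The section on text message surveys also lists CCT school attendance as survey content, which sides with Data Collection. The second contrast, 6 against 12 months, is free of the problem if both surveys use the same mode.

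**Step 2. Is a same-mode baseline already planned?** Study Outcomes schedules text/USSD self-report at 0, 3, 6, 9 and 12 months in the HIV-positive cohort, but for ART adherence. It does not say that the month-0 text survey carries the risk items. No month-0 text survey is stated for the PrEP cohort.

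**Step 3. The plan's own power figures.** Participants and Sample Size assumes 80% retention: 100 × 0.8 = 80 HIV-positive, 50 × 0.8 = 40 PrEP and 50 × 0.8 = 40 CCT. For a paired t test, power = P(|T| > t₀.₉₇₅,ₙ₋₁), where T is noncentral t with n − 1 degrees of freedom and noncentrality d√n. The article does not state alpha or sidedness; I take two-sided 5%.
- n = 80, d = 0.33: noncentrality 0.33 × √80 = 2.95, power 83.0% (stated 83%).
- n = 40, d = 0.45: noncentrality 0.45 × √40 = 2.85, power 79.3% (stated 80%).

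Both reproduce to within a point. One-sided 5% gives 90.0% and 87.5%, which do not match. These figures are stated for ART adherence and school attendance, not for risk behavior. They serve here only to check the formula and supply the numbers of pairs.

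**Step 4. Illustration of a pure mode shift.** Set the true change to zero and let the mode move the mean paired difference by m standard deviations of that difference. The chance of a significant result is the same formula with d = m. The values of m are assumed.

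| Assumed m | 80 pairs | 40 pairs |
|---|---|---|
| 0 | 5% | 5% |
| 0.1 | 14.3% | 9.5% |
| 0.2 | 42.4% | 23.5% |
| 0.33 | 83.0% | 53.0% |

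To more places, the 40-pair entries for 0.1 and 0.2 are 0.0946 and 0.2346, so they round to 9% and 23%.

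**The case against.** The strongest reply has five parts.

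*Not every cohort is affected.* A reader might infer that all three cohorts switch from tablet interview to text. The documents do not support that. The CCT schedule has in-person CAPI at every visit, so on that text nothing switches. The PrEP cohort is seen in person as well as by text, and the article adds that SMS and/or USSD and CAPI surveys will be given to the cohorts generally. This stands, and it confines the evident confound to the HIV-positive cohort and the probable one to PrEP.

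*The remedy may already exist.* The month-0 text survey for ART adherence might be the standard 10-question survey, with the risk items included. This is possible but not stated, and the Results section does not name it as the baseline.

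*Sensitive items can be answered privately at baseline.* This narrows the difference between modes. Interviewer presence, setting, length and device still differ, so it is a reason to expect a smaller shift, not none.

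*The size is hypothetical.* This also stands. Nothing in the article gives a mode effect, and the Results section speaks of estimating changes in risk behavior, not of a paired t test. A reader might take the percentages in the table as this plan's false-positive rates; they are not.

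*The stakes are limited, and the detailed plan is not shown.* Risk compensation is in the abstract but not among the listed objectives, and sexual risk exposure is an outcome for the PrEP cohort only. The cohorts' stated main purpose is feasibility. The unseen evaluation plan (Multimedia Appendix 2) may specify the instruments. It cannot, however, recover a same-mode baseline if none was collected.

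**Conclusion.** The point holds for the HIV-positive cohort, where the evident comparison is CAPI at baseline against SMS/USSD at 6 months. It probably holds for the PrEP cohort, depending on which source supplies the 6-month value. There, an initial change in reported risk behavior cannot be attributed to behavior rather than mode. For the CCT cohort the finding is an internal contradiction about follow-up mode, not an established switch.

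The direction and size of any mode effect are unknown. On the assumptions in Step 4, even a shift of 0.1 SD raises the chance of a spurious significant change above the nominal 5%, and a shift of 0.33 SD makes it more likely than not at either sample size. The conclusion does not depend on those figures. It rests on the stated modes, on the absence of a comparator, and on no same-mode month-0 measure of risk behavior being stated.

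Feasibility, uptake and coverage are untouched. ART adherence is not affected in the same way, because it has a month-0 text self-report. The matter should be settled before enrolment, since a missing baseline cannot be collected later.

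**What to change.** 1. In the HIV-positive and PrEP cohorts, include the same risk-behavior items in a month-0 SMS/USSD survey as in the later ones. The month-0 text self-report of ART adherence already planned for the HIV-positive cohort is a natural vehicle.
2. State in the Results section that this month-0 value is the baseline for change estimates, that the 6- and 12-month values come from the same survey, and that the CAPI baseline is used for description. This also fixes the PrEP 6-month source.
3. Reconcile Cohort Follow-Up Schedules, Data Collection and the section on text message surveys so that the CCT cohort uses one mode at every time point, baseline included.

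The cost is one extra 10-question text survey for about 150 participants (100 HIV-positive + 50 PrEP), who are to be given study phones in any case, plus the wording changes. If a month-0 text survey cannot be added, report the baseline-to-6-month change as confounded with mode and rest statements about behavior change on the 6-to-12-month contrast.

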## Discussion

### Principal Findings

The MP3 Youth study designed and created a protocol to pilot and evaluate a gender- and youth-specific combination HIV prevention study in Kenya. We propose that offering youth a combination of HIV prevention interventions in a mobile health setting will be convenient and effective based on our preliminary research. Our formative research indicated that youth are interested in receiving multiple services in one place. We anticipate that the results of the exit interview we will conduct at the mobile events will yield positive feedback on the delivery of the interventions as the events will be conveniently located and youth friendly. Cross-sectional analyses of the mobile health data will provide insights into the uptake of interventions and feasibility of offering them in a one-stop-shop integrated services delivery modality. The results of the longitudinal cohort data will provide innovative information on the potential impact of the interventions and the behavioral changes among the cohort participants over time. The pilot study will give new insights into how components do or do not fit together in a real-world combination prevention package. The results of the pilot will then be used to refine the design of an effectiveness trial or a large-scale program evaluation.

MP3 Youth is one of the few combination HIV prevention interventions incorporating elements of behavioral, biomedical, and structural interventions in one delivery setting and developed for youth. Despite the fact that youth are both at highest risk for HIV and the largest proportion of the global population, only recently have they been targeted for comprehensive HIV prevention interventions.

The mobile health event strategy outlined in this protocol to identify youth is unique. We were able to use the information gleaned from focus groups to target the location and delivery of services and to use the literature and lessons learned from previous studies to design a protocol to deliver evidence-based interventions that are youth-friendly and gender-sensitive. The logistics of implementing mobile health events for 10 days at a time will involve setting up and breaking down a clinic that is completely equipped to handle HIV testing, CD4 and viral load analysis, family planning, a surgical theatre for male circumcision, and a pharmacy. This strategy will be effective for reaching youth who are at risk and in need of a variety of services. We will enroll participants using biometrics. This strategy will allow us to track participant flow and uptake of services during the mobile events. Biometrics will also allow us to successfully identify participants during follow-up visits [69].

### Limitations

This is a pilot feasibility study using mixed-methods (mathematical modeling, qualitative data, cross-sectional, and longitudinal cohort elements). As this pilot study does not employ a controlled trial design or comparator, population-level effectiveness of the combination HIV prevention approach cannot be determined. The logistics required to implement a combination HIV prevention study may be expensive and may require a lot of up front staff and referral partner capacity building that may delay implementation.

### Conclusion

The MP3 Youth lessons learned will provide real-world contributions to implementation science regarding uptake of combination prevention. Some of the preliminary lessons learned in developing the protocol were considered as part of the Kenya national health strategy; one of the 8 countries participating in the PEPFAR DREAMS initiative. The analyses conducted for MP3 Youth will be key in highlighting evidence for a scaled-up youth prioritized HIV/AIDS strategy in Kenya and other high HIV burden settings.

## Appendix

Multimedia Appendix 1 Logic Model.

Multimedia Appendix 2 Evaluation plan.

## Abbreviations

ART: antiretroviral therapy
CAPI: computer-assisted personal interview
CCT: conditional cash transfer
CD4: cluster of differentiation 4
cRCT: clustered randomized controlled trial
DBS: dried blood spots
eCAP: electronic medication vial
HepBsAg: hepatitis B surface antigen
HIV: human immunodeficiency virus
IRB: institutional review board
iRCT: individually randomized controlled trials
PrEP: pre-exposure prophylaxis
SSA: sub-Saharan Africa
TDF/FTC: tenofovir disoproxil fumarate/emtricitabine
USSD: unstructured supplementary service data
